# Population

The population will comprise frontline healthcare workers selected to be representative of all departments at Great Ormond Street Hospital. We will ensure that that age ranges and sex are representative of the trust population age distribution. The age distribution of the participants will be checked during recruitment against the known age distribution of the hospital to ensure a representative sample. If significant differences among ages between the study population and the hospital population age range emerge, the study will actively recruit age ranges underrepresented. If participants leave the GOSH NHS trust during the study they will remain eligible to continue in the study. Their contact details will be updated on follow-up questionnaires.

## Inclusion Criteria (See Also Study Flow Diagram, page 18 )

***SARS-CoV-2 Seropositive Cases N ~ 2100***

- Healthcare worker at GOSH (other UK and European Hospital Healthcare workers at their corresponding sites)
- ≥18 years of age
- ALL have confirmed detectable antibodies to SARS-CoV-2 infection on baseline screen

Then 1 of:

**Core Group of PCR Confirmed Cases**

## Symptoms consistent with SARS-CoV-2 infection and SARS-CoV-2 PCR Positive N ~ 400

OR

**Other SARS-CoV-2 Sero-positives N ~ 1700**

B) Symptoms consistent with SARS-CoV-2 infection and SARS-CoV-2 PCR Negative cases

OR

C) No symptoms consistent with SARS-CoV-2 infection and PCR Not Tested cases

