Within this initial planned cohort (**Study Flow Diagram 1, page 18**), a subset of ~400 staff members with confirmed symptomatic, PCR positive, antibody positive or equivocal, SARS-CoV-2 disease (and an additional 2100 staff sero-positive or equivocal staff members who were either PCR negative or asymptomatic) will be followed with intensive 1 to 2 monthly blood sampling to determine antibody titres to the SARS-CoV-2 specific protein using the *EDI^TM^* ELISA assay. Participants who are seropositive or equivocal will also have the option of providing an additional one off 20ml sample for T-cell assay analysis and a salivary sample for IgA analysis.

All 7000 recruited healthcare workers (2100 SARS-CoV-2 sero-positives and N~4900 seronegatives) will have blood taken for serological testing at baseline then at 6-monthly intervals for a total of 6 years. In addition to repeated serological testing, participants will continue as all healthcare workers at GOSH to have access to the staff testing program. This program tests symptomatic staff members by nasal swab PCR testing for SARS-CoV-2. Staff who have been tested for SARS-CoV-2 through the staff testing program will be consented for the PCR and serology results to be used in the study. All participants will also be asked to complete a detailed health and demographic questionnaire prior to each appointment, electronically. The technology design of the questionnaire will optimise participation. If key questions are missed, participants will be contacted by phone, text or email to optimise data collection and statistical analysis. As key factors impacting COVID-19 evolve, questions on review questionnaires will address these.

The data will enable us to determine the attack rate (percentage of healthcare workers with PCR proven infections/re-infections) and incidence (the rate of occurrence of disease) of SARS-CoV-2 infection amongst healthcare workers with and without antibodies. The comparison of the attack rate will indicate the protection antibodies provide. Further, the stratification of results by antibody titres, will provide information on whether a specific level of antibody confers protection.

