**Core Comparison Group N ~ 4200**

## Have not had clinical symptoms consistent with SARS-CoV-2 infection*

OR

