**Other Seronegatives N ~ 700**

B) Have had sympoms of SARS-CoV-2 infection but have been tested and were PCR positive or negative but have not developed antibodies at 21 days

*Clinical Symptoms for SARS-CoV-2 infection are defined as one of:

1) New and persistent cough

2) Confirmed temperatures of 37.8 and above

3) Anosmia or altered taste sensation

4) Extreme fatigue

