## Screening and Eligibility Assessment

Screening of potential applicants by study staff will occur when they attend the consent meeting (either face to face, by telephone or by zoom meeting). The process is simple and only involves ensuring that two criteria are met.

1. Either the staff member has had symptoms of possible, probable or confirmed SARS-CoV-2 infection (as defined in this protocol) and must wait for completion of 21 days from symptom onset before entering the study

OR

1. The staff member is asymptomatic but has been exposed to someone with suspected or confirmed SARS-CoV-2 infection and must wait for the completion of 21 days from the start of this exposure
2. The staff member has not had exposure to or symptoms consistent with SARS-CoV-2 infection so can enter the study immediately

Once eligibility has been confirmed, informed consent will be sought and an informed consent document completed and signed off (either face to face by the study participant or, if consent is not taken in person, then by two trained members of the study team). Study participants will then be directed to an online survey (health questionnaire) which they will need to complete to prior to arranging an appointment with the phlebotomy team for blood sampling.

All staff at GOSH will also be asked if they would like to be made aware of other parallel COVID related studies running at GOSH and UCL. If they express interest in this then they will be directed to the relevant study websites/email addresses.

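### The section 8.1 groups do not cover every combination of serology, symptoms and PCR status, and are narrower than the synopsis and sections 7.1 and 9.3

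*Protocol*

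**What the plan says.** Section 8.1 splits the cohort by baseline serology and then requires one of the listed groups.

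- **Seropositive arm (about 2100).** The groups are "Symptoms consistent with SARS-CoV-2 infection and SARS-CoV-2 PCR Positive N ~ 400", "Symptoms consistent with SARS-CoV-2 infection and SARS-CoV-2 PCR Negative cases" and "No symptoms consistent with SARS-CoV-2 infection and PCR Not Tested cases". The last two together make up about 1700.
- **Seronegative arm (about 4900).** About 4200 "Have not had clinical symptoms consistent with SARS-CoV-2 infection", with no PCR condition. About 700 "Have had sympoms of SARS-CoV-2 infection but have been tested and were PCR positive or negative" and had no antibodies at 21 days.
- **Serology.** One arm requires confirmed detectable antibodies at baseline, the other a confirmed negative result.

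Other sections are wider.

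- The Study Synopsis takes all adult healthcare workers at the hospital apart from listed exclusions, none of which concerns PCR.
- Section 9.3 lets a person enter 21 days after onset if "the staff member has had symptoms of possible, probable or confirmed SARS-CoV-2 infection", again without a PCR condition.
- Section 7.1 describes the core group as "confirmed symptomatic, PCR positive, antibody positive or equivocal, SARS-CoV-2 disease". It describes the remaining seropositive or equivocal staff as PCR negative or asymptomatic, without requiring the asymptomatic to be untested.

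**The concern.** The rule that sorts people into groups has holes that the rules admitting them do not have. Screening under 9.3 does not ask for a PCR result, and a group can be assigned only once baseline serology is known. A person can therefore be screened in, consented and bled, and only then turn out to belong nowhere.

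At stake are who counts as a participant and what secondary objective 1 estimates. That objective asks what share of wholly asymptomatic staff have antibodies. Under 8.1, asymptomatic staff with a PCR result stay in when seronegative and fall out when seropositive. This selection depends on the outcome being measured.

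**Working it through.** **1. The plan's own totals.** From section 8.1: 400 + 1700 = 2100; 4200 + 700 = 4900; 2100 + 4900 = 7000. These agree with the stated arm and cohort sizes, so the plan treats the groups as complete. (Section 7.1 counts the other seropositives as an additional 2100, which would give 2500. That is a separate discrepancy and is not used here.)

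**2. Enumeration.** Two serostatus levels × two symptom levels × three PCR states = 12 cells.

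| Serology | Symptoms | PCR positive | PCR negative | Not tested |
|---|---|---|---|---|
| Positive | Yes | A | B | none |
| Positive | No | none | none | C |
| Negative | Yes | B | B | none |
| Negative | No | A | A | A |

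Four of the 12 cells have no group: three seropositive and one seronegative. Equivocal serology lies outside the table, because it satisfies neither arm's criterion.

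**3. Effect on the asymptomatic proportion if 8.1 is applied literally.** Let C be the size of seropositive group C, T the omitted asymptomatic PCR-tested seropositives, and U the omitted symptomatic untested seropositives. The protocol gives none of these, only B + C of about 1700. All values below are assumptions.

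*Denominator: asymptomatic staff (wording of secondary objective 1).* The observed share is C/(C + 4200). The complete share is (C + T)/(C + T + 4200). U does not appear. The observed share is lower whenever T > 0.

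| C | T | Observed | Complete |
|---|---|---|---|
| 800 | 0 | 16.0% | 16.0% |
| 800 | 50 | 16.0% | 16.8% |
| 800 | 100 | 800/5000 = 16.0% | 900/5100 = 17.6% |
| 800 | 300 | 16.0% | 1100/5300 = 20.8% |
| 400 | 300 | 400/4600 = 8.7% | 700/4900 = 14.3% |
| 1200 | 300 | 1200/5400 = 22.2% | 1500/5700 = 26.3% |

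*Denominator: seropositives (section 5.1 also speaks of the percentage of infections that are asymptomatic).* The observed share is C/2100. The complete share is (C + T)/(2100 + U + T). The observed share is too low only if T/(T + U) > C/2100, that is, if T/U > C/(2100 − C). It is too high if the inequality is reversed.

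| C | U | T | Observed | Complete | Error |
|---|---|---|---|---|---|
| 800 | 300 | 0 | 38.1% | 800/2400 = 33.3% | +4.8 points |
| 800 | 300 | 100 | 38.1% | 900/2500 = 36.0% | +2.1 points |
| 800 | 50 | 300 | 38.1% | 1100/2450 = 44.9% | −6.8 points |

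The break-even T/U is 400/1700 = 0.24, 800/1300 = 0.62 and 1200/900 = 1.33 for C = 400, 800 and 1200. The two gaps pull in opposite directions here.

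**The case against.** The strongest reply is that the groups are descriptive and nothing depends on them. The synopsis and section 9.3 admit these people, and section 8.2 excludes nobody on PCR status. Section 9.1 assigns follow-up by the arm in which the serology result places a person. Section 9.5 sets visit frequency by serostatus, and the attack-rate power calculation in section 12.1 compares 2100 with 4900 on serostatus alone. Secondary objective 1 carries no PCR condition and nowhere names group C as its numerator. An analyst following the objective would count asymptomatic PCR-tested seropositives, and the bias would not arise.

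Much of this stands. A reader might infer that eligible staff will certainly be excluded, or that visits will be allocated ad hoc. The documents support neither: exclusion depends on which section governs, and membership of B or C changes no visit and no stated comparison. A reader might also infer that both gaps push the asymptomatic proportion down. The symptomatic-untested gap never does so: it is irrelevant to one denominator and pushes the other up. Section 7.1 says the staff programme swabs symptomatic staff, so T may be small. Section 9.4 does record home kits and earlier tests, so T cannot be taken as zero.

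The reply does not remove the contradiction. Section 8.1 is the inclusion rule and is worded as a requirement, while other sections admit or follow people who fail it. The flow diagrams are not visible in the text at hand, so whether they place the missing cells could not be checked.

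**Conclusion.** The point holds as a contradiction between the inclusion criteria and the rest of the protocol. Four of the 12 combinations have no group, and equivocal results have no arm in 8.1. Loss of eligible staff after consent and sampling follows only if 8.1 is read literally.

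Under that reading, the antibody-positive share of asymptomatic staff is biased downward to the extent that asymptomatic PCR-tested seropositives exist. In the assumed cases above, the shortfall runs from nothing (T = 0) to 5.6 points (C = 400, T = 300). The asymptomatic share of infections may err in either direction. No figure in the protocol fixes T, U or C, so these numbers show direction and sensitivity only and are not estimates. A general claim of downward bias is not supported. The primary objective's core group of symptomatic, PCR-positive cases is untouched by the four missing cells, although section 7.1 admits equivocal results to it and 8.1 does not.

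**What to change.** - Make the groups in 8.1 exhaustive. Seropositive B: symptoms, PCR negative or not tested. Seropositive C: no symptoms, any PCR status. Seronegative B: symptoms, any PCR status including not tested.
- State in 8.1 where equivocal results belong, consistently with section 7.1.
- Align the Study Synopsis and sections 7.1, 8.1 and 9.3, and check the flow diagrams against them.
- Define the numerator and denominator of secondary objective 1 by symptoms and serostatus, regardless of PCR testing. Say whether the asymptomatic share of infections in section 5.1 is a separate quantity.

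The cost is wording only. No extra visit, sample or questionnaire item is needed.

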***SARS-CoV-2 Seronegative Comparison Group N ~ 4900***

- Healthcare worker at GOSH (other UK and European Hospital Healthcare workers at corresponding sites)
- ≥18 years of age
- ALL have confirmed negative antibodies to SARS-CoV-2 infection on baseline screen

Then 1 of:

**Core Comparison Group N ~ 4200**

## Have not had clinical symptoms consistent with SARS-CoV-2 infection*

OR

**Other Seronegatives N ~ 700**

B) Have had sympoms of SARS-CoV-2 infection but have been tested and were PCR positive or negative but have not developed antibodies at 21 days

*Clinical Symptoms for SARS-CoV-2 infection are defined as one of:

1) New and persistent cough

2) Confirmed temperatures of 37.8 and above

3) Anosmia or altered taste sensation

4) Extreme fatigue

## 8.2 Exclusion Criteria

- <18 years of age
- On immunosuppressive or immunomodulatory medication that may impact test reliability
- Received any blood product including immunoglobulins after September 2019
- Has received convalescent sera as treatment
- Current diagnosis of a malignancy that may impact test reliability
- Those lacking capacity to provide informed consent

**8.3 Study Flow Diagram 1**

[figure not shown]

# Study Procedures

## Recruitment

The trust communications team will send an all staff email to inform them about this research project with an invitation link to read the information and eligibility criteria. The microbiology/infection control department at GOSH will also send out a communication to all GOSH staff who have tested positive (or negative) for SARS-CoV-2 as part of the staff testing program to raise awareness of the study and provide the option to join . This approach will permit the dissemination of study to the core study group without study staff having access to identifiable information. We will also consent staff for the use of stored serum and PCR samples taken as part of this staff testing program for use in future research. This component is optional. The positive arm of the study (and negative controls) will have the option of providing a 20ml in EDTA sample for T-cell assay studies, and a salivary sample for IgA analysis, both for research purposes. As these are research tests, results of these extra assays will not be provided to participants. They will be formally consented for this.

Informed consent will then take place in person (or if preferred by telephone or using a zoom meeting). During the informed consent process participants will be provided with information and the chance to answer questions they may have about the study. We will not require the use of any resources or medical records to identify study staff as they are colleagues within the same hospital trust as the study investigators. We will ensure that recruited populations are representative of staff at GOSH (which has a slight majority of women) and that age ranges are representative of the trust population age distribution.

If the participant prefers to undertake a telephone or zoom consent (to maintain physical distancing) we will follow established GOSH trust guidelines. Telephone consent will be witnessed by another member of study staff and co-signed. Study staff undertaking consent will confirm the name and date of birth of the participant without stating their name. At the end of the conversation the witnessing member of staff will speak to the participant to confirm that they have agreed to join the study, then co-sign the document.

After informed consent is completed, participants undertake an online health questionnaire before booking an appointment at the study-run phelobotomy clinic for serological testing. Results of the serological testing will be returned to the participants by secure trust e-mail or via text. We will carefully describe the meaning and significance of a positive, equivocal and negative test in the automated results email as described on the participant information sheet. After returning results, participants will be invited to a follow up appointment in 1 to 2 months or 6 months depending on which arm of the study their results place them in. Early experience established that a small minority of staff (particularly the temporary catering, cleaning and portering staff) do not have trust e-mails. If this is the case, these participants will be asked if they would be happy to receive their serology results over the phone, verbally or by text message; if this is not feasible, we will ask to send their results to their personal email address or to have them collected in person from the study team.

## Informed Consent

Only Good Clinical Practice certified, Human Tissue Act trained, study trained personel who have undertaken the GOSH specific consent training modules and are registered in the study log will be permitted to obtain informed consent. All those who have completed training and are able and eligible to undertake informed consent will be named by the CI/PI on the study log. A detailed information sheet has been prepared (Appendix C: Study Information Sheet). In lay terms this document details the rationale for the study, how and why the participant has been identified and what will happen if potential participants enrol in the study. The information sheet clearly documents the possible inconveniences and benefits of being involved in the study, that enrolling in the study is completely optional and that withdrawl from the study at any stage is also possible at any time.

The secure management of study data is discussed along with the steps taken to minimize the risk of a breach of data security. As this study involves the storage of blood samples for testing and for future work the information sheet explains this in a dedicated section on tissue storage and generic consent for future research. Potential participants will be allowed as much time as they need to decide whether or not they wish to participate in the study.

## Screening and Eligibility Assessment

Screening of potential applicants by study staff will occur when they attend the consent meeting (either face to face, by telephone or by zoom meeting). The process is simple and only involves ensuring that two criteria are met.

1. Either the staff member has had symptoms of possible, probable or confirmed SARS-CoV-2 infection (as defined in this protocol) and must wait for completion of 21 days from symptom onset before entering the study

OR

1. The staff member is asymptomatic but has been exposed to someone with suspected or confirmed SARS-CoV-2 infection and must wait for the completion of 21 days from the start of this exposure
2. The staff member has not had exposure to or symptoms consistent with SARS-CoV-2 infection so can enter the study immediately

Once eligibility has been confirmed, informed consent will be sought and an informed consent document completed and signed off (either face to face by the study participant or, if consent is not taken in person, then by two trained members of the study team). Study participants will then be directed to an online survey (health questionnaire) which they will need to complete to prior to arranging an appointment with the phlebotomy team for blood sampling.

All staff at GOSH will also be asked if they would like to be made aware of other parallel COVID related studies running at GOSH and UCL. If they express interest in this then they will be directed to the relevant study websites/email addresses.

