## Introduction

## Background and Rationale

Since appearing as a cluster of patients with ARDS in the December of 2019 in Wuhan, China, COVID-19 caused by SARS-CoV-2 has rapidly spread worldwide, with pandemic status declared in March 2020.^1^ Currently there have been over 1.6million cases, with over 100, 000 deaths.^2^

SARS-CoV-2 is a β-coronavirus, an enveloped non-segmented positive-sense RNA virus.^3^

Sequencing has demonstrated that SARS-CoV2 is 79% identical to SARS-CoV, which caused the SARS (Severe Acute Respiratory Syndrome) epidemic in 2003, 50% with the MERS (Middle Eastern Respiratory Syndrome) coronavirus and 96% identical to a bat coronavirus.^4,5^ Analysis of 104 strains of samples taken between December and February demonstrated 99.9% homology, with little mutation, providing some hope for eventual vaccine therapy.^6,^ ^5^

The virus was first recognised in Wuhan, China. Though many of the initial cases were linked to a seafood market, a significant proportion of early cases did not have any association with the market, suggestive that human to human spread occurred in the month prior.^1^

In contrast to the related coronavirus respiratory diseases MERS and SARS, which were more frequently associated with nosocomial infections, COVID-19 spreads more avidly, via close contacts, with a household secondary attack rate of 3-5%.^7,6^ Early calculations of the reproductive number (R_0_) were estimated at 2.3-3.5.^8^ The viral load profile is similar to influenza, peaking early together with symptom onset, which could account for the higher transmissibility compared with SARS and MERS.^9^ The virus is spread through respiratory droplet and fomite spread in close proximity contact and via aerosolised procedures, a particular risk to health care workers. The virus has also been isolated in faecal samples, however no known cases of faecal-oral spread have been noted.^10,11^ Similarly to SARS-CoV, SARS-CoV-2 gains entry into respiratory epithelial cells via attachment to the ACE2 receptor.^4,12^ The clinical presentation and pathology resembles SARS and MERS, though with less upper respiratory and gastrointestinal symptoms.^13^ The estimated incubation period has a mean of 5 days, with the majority of cases developing symptoms by 14 days.^14^ However one study found 15.6% of patients had not developed symptoms by day 14 following exposure.^15^

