- Zhang’s study of 222 patients in Wuhan during the convalescent stage (within 35 days) found 98.6% had IgG detected and 82% had IgM detected. IgG was first detected on day 4 of illness and peaked in the 4^th^ week, IgM was first detected on day 3 of illness and peaked in the 2^nd^ week.^31^
- Lou et al tested eighty patients (confirmed on PCR with deep sputum samples) using ELISA, lateral flow assays and CMIA (chemiluminescence microparticle immunoassays). ELISA performed the best of all three tests but the difference was not found to be significant. IgM and IgG seroconversion occurred at 10- and 12-days post symptom onset respectively. Antibody levels increased rapidly after day 6 post onset and by day 21 IgM seroconversion was 100% and by day 29 IgG was 97.1% (93.3% at 21days). Decline of viral load co-occurred with the rising antibody levels. At day 14 post exposure 45.5% had seroconverted. Keeping note of isolation duration times, 15.6% did not present with symptoms prior to 14 days post exposure.^15^
- To’s study of 23 patients, found at 14 days seropositivity against internal nucleoprotein (NP) was 94% for IgG and 88% for IgM. Against nucleo-capsid protein receptor binding domain (RBD), it was 100% for IgG and 94% for IgM. More patients seroconverted to IgG before IgM for both types, but this may be due to reduced sensitivity of the IgM EIA. Viral load was inversely related to antibody response. However in Zhao’s study three critical patients did not have a decline in viral load associated with increasing antibody titres.^32^ Most patients developed antibodies around day ten, one patient with severe disease developed antibodies at day 6. No genomic mutations were detected on serial sampling from four patients.^9^
- Zhao studied 173 patients and found whilst in the first 7 days following onset, PCR was more sensitive than serological tests (66.7% vs 38%), By day 12 seroconversion rates were 90% whilst PCR detection was 54% and by days 15-30 PCR detection was 45.5%. Of the patients that did not seroconvert – all samples were taken before day 13 of symptom onset.^32^ Thus, serology is especially important for patients that present late, with viral loads below the detection limit of RT-PCR.^9^

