## Subsequent Visits

Subsequent follow-up visits will be explained to all potential study participants as part of the informed consent process. The 2100 seropositive serology cohort will be followed intensively every 1 to 2 months for repeated serological testing whilst the 4900 seronegative comparison group will be followed 6 monthly. Participants from the positive arm of the study (as well as negative controls) will have the option of providing a 20ml in EDTA sample for T-cell assay studies and tissue typing, and a salivary sample for IgA analysis, both for research purposes. As these extra assays are research tests, results will not be provided to particpants. They will be formally consented for this.

After the initial intensive phase, all ~7000 recruits will be followed 6 monthly for the 6 year duration of the study. Follow-up visits will be arranged following the baseline assessment. The same blood tests 4ml EDTA and 4ml serum will be taken at each follow up appointment as well as the same symptom questionnaire. If a COVID-19 vaccination becomes available during the study we will undertake performance evaluation of an ELISA suitable for monitoring antibody titres to the vaccine target. We will then continue to follow up our cohort with the additional focus on the antibody titres to vaccination, duration of immunity following vaccination and the attack rate in the vaccinated and unvaccinated groups (with the previso that we expect the vaccine will have wide and rapid uptake).

Further detailed questionnaires will be sent to subgroups found to have higher incidence of infection, to further delineate the susceptibility and exposure factors.

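### The 21-day wait before baseline serology runs from symptom onset in symptomatic staff but from the start of exposure in asymptomatic staff, so a larger share of infected asymptomatic staff is filed as seronegative

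*Protocol*

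**What the plan says.** Section 9.3 sets two waiting rules of equal length. A staff member with symptoms "must wait for completion of 21 days from symptom onset before entering the study". One without symptoms but with a known exposure "must wait for the completion of 21 days from the start of this exposure". Both are minimum waits: consent comes next, then a questionnaire "which they will need to complete to prior to arranging an appointment with the phlebotomy team for blood sampling".

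The kinetics are in section 5.1 (Background and Rationale):
- Incubation: "The estimated incubation period has a mean of 5 days, with the majority of cases developing symptoms by 14 days". One cited study found 15.6% still without symptoms on day 14 after exposure.
- IgG on the onset clock: seroconversion at 12 days in one study and a median of 14 days in another; 93.3% positive at day 21 and 97.1% at day 29.
- On the exposure clock: "At day 14 post exposure 45.5% had seroconverted".

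The baseline result then sets the follow-up. Under section 9.5 (Subsequent Visits), "the 4900 seronegative comparison group will be followed 6 monthly", while seropositive staff return every 1 to 2 months. The Core Comparison Group in section 8.1 (about 4200 people) consists of seronegatives who "Have not had clinical symptoms consistent with SARS-CoV-2 infection".

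**The concern.** The same 21 days is counted from two different events. Onset follows infection by the incubation period, so the asymptomatic rule allows less time for antibodies to appear. It is shorter again when infection happens some days after the exposure began, which is plausible in a workforce that section 5.1 describes as exposed repeatedly.

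The shortfall depends on symptom status, and that makes it more than ordinary test insensitivity:
- **Secondary objective 1** estimates the proportion of asymptomatic staff with antibodies. Infected people sampled too early are counted as negative, so the estimate is biased downward.
- **Secondary objective 2** compares attack rates with and without antibodies. If past infection protects, infected people placed in the seronegative group lower its attack rate and shrink the contrast.
- **Seroconversion rates**, which section 5.1 also wants to learn, are misdated when a person infected before baseline first tests positive at month 6.

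**Working it through.** The protocol states no figure that depends on this point, so there is nothing to reproduce. The check applies the section 5.1 kinetics to both clocks.

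**Assumptions.** Kinetics reported in patients carry over to asymptomatic people, with an onset-equivalent date in place of onset. The first study's 12 days is treated as a median. The 45.5% is treated as comparable with the IgG figures.

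**1. Equivalent day.** For infection on the first day of exposure, 21 − 5 = day 16 after the onset-equivalent. For infection L days later it is day 16 − L.

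**2. Symptomatic staff at the minimum wait.** 100% − 93.3% = 6.7% missed.

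**3. Asymptomatic staff infected on the first day, by linear interpolation.**
- From 50% at day 12 to 93.3% at day 21 after onset: 50 + 43.3 × 4/9 = 69.2% positive at day 16.
- From 50% at day 14 to 93.3% at day 21: 50 + 43.3 × 2/7 = 62.4%.
- On the exposure clock, from 45.5% at day 14 to 93.3% at day 26 (21 + 5): 45.5 + 47.8 × 7/12 = 73.4%.

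**4. The same by simulation** (1,000,000 draws per setting). Time from infection to IgG = incubation + time from onset to IgG.
- Onset to IgG: lognormal, median 12 or 14 days, with log-SD = ln(21/median)/z(0.933). This gives ln(21/12)/1.4985 = 0.373 and ln(21/14)/1.4985 = 0.271.
- Incubation: lognormal with mean 5 days and assumed log-SD 0.4, 0.6 or 0.8; or an assumed median of 5 days with 15.6% beyond day 14.

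| Infection relative to start of exposure | IgG positive at day 21 from start | Missed |
| --- | --- | --- |
| First day | 55% to 76% | 24% to 45% |
| 3 days later | 36% to 59% | 41% to 64% |
| 7 days later | 9% to 31% | 69% to 91% |
| Spread evenly over 14 days | 18% to 33% | 67% to 82% |

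For infection on the first day, the missed share is 24/6.7 = 3.6 to 45/6.7 = 6.7 times that in symptomatic staff.

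**5. Fit.** The model gives 99.1% to 99.6% positive at day 29 after onset (quoted: 97.1%) but only 9% to 31% at day 14 after exposure (quoted: 45.5%). It is therefore pessimistic early on the exposure clock. The interpolation anchored on 45.5% avoids this and still leaves 26.6% missed, 26.6/6.7 = 4.0 times the symptomatic figure.

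**6. What corrects a false negative.** Sections 9.1 and 9.5 give no repeat serology before 6 months after a negative result. Section 7.1 limits the staff PCR programme to people with symptoms. In section 8.1, symptomatic seronegatives must have had no antibodies at 21 days; the Core Comparison Group has no matching condition.

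**The case against.** Several points on the other side stand.

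- A reader might infer that recently infected asymptomatic staff are, in general, tested before they seroconvert. The documents do not support that. The quoted IgG times of 12 and 14 days fall before the day-16 equivalent, so most people infected on the first day would already be positive. Most are missed only when infection comes several days into a continuing exposure, and the protocol gives no exposure duration.
- The 21 days is a minimum. Consent, questionnaire and booking follow, so actual samples are later.
- It is tempting to take a 14-day incubation, place the sample at day 7 after onset, and apply the 38% serological sensitivity in section 5.1. But someone who develops symptoms moves to the onset rule, and the 38% covers the whole first week, not day 7.
- Symptomatic staff are missed too (6.7%). The difference is one of degree.
- A reader might infer that a first positive serology at month 6 would count as a new infection in the attack rate. It would not: section 7.1 bases the attack rate, and section 12.1 the survival event, on PCR-proven infection.
- Equivocal results go to 1 to 2 monthly sampling, which may catch some rising titres.
- Section 5.1 itself says that little is known about asymptomatic, non-hospitalised people, so carrying the kinetics over is an assumption.

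None of this removes the unequal clocks or the gap in expected sensitivity between the two groups.

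**Conclusion.** The point holds as a differential misclassification of moderate importance. At the minimum wait, roughly 24% to 45% of asymptomatic staff infected on the first day of exposure would still be IgG-negative, against 6.7% of symptomatic staff, and more if infection occurs later. This rests on patient kinetics applying to asymptomatic people and on the assumed incubation spread.

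The direction for secondary objective 1 is downward. For secondary objective 2, dilution is possible and depends on whether infection protects. Seroconversions found at month 6 may be misdated but are not attack-rate events. The bias in either objective cannot be sized, because the number of recently exposed, infected, asymptomatic staff is not given. The primary objective concerns proven cases and is little affected. The timing of the baseline sample is an enrolment rule; analysis cannot later supply a sample that was not taken.

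**What to change.** In section 9.3:

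1. **Discrete exposure, no symptoms.** Count the wait from the last exposure and add an incubation allowance from section 5.1, between the 5-day mean and 14 days. That gives 21 + 5 = 26 to 21 + 14 = 35 days, so that both rules approximate 21 days after onset. At day 26 after infection the simulated share positive is 75% to 92%. The mean allowance therefore narrows the gap without fully closing it.
2. **Continuing exposure.** Enrol as now, record the last exposure date in the questionnaire, and keep these staff in the main estimate. Excluding them from objective 1 would remove people plausibly at higher risk of silent infection.
3. **Sensitivity analysis for objectives 1 and 2.** Set aside seronegatives sampled within that window or, for objective 2, start their at-risk time at the next negative sample. For objective 1, removing only negatives raises the proportion, so read the result as an upper comparison beside the main estimate.

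Cost: about 1 to 2 weeks' later entry for staff with a recent discrete exposure (plus the length of that exposure if it lasted more than a day), one extra questionnaire date, and one sensitivity analysis.
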